### Data collection

#### Study plan

One day before surgery, a research assistant will identify eligible patients and inform them about the procedures and study aims. During the study, patients can withdraw their consent at any time. If the surgery is cancelled or the exclusion criteria are met, the patient will be excluded. Figure 1 shows the study flowchart.

**Figure 1 F1:**
[figure not shown]
Study flowchart.

Candidate predictors are selected based on published data,^14^ professional knowledge and clinical expertise. The following clinical variables will be recorded in the case report forms (online supplemental file 2). The research assistant will fill out the preoperative potential predictors section of the form during the preoperative visit, and document variables in the intraoperative potential predictors section and values of heart rate (HR) and non-invasive cuff blood pressure (NIBP) in the outcome section during the case when looking at the monitor.

10.1136/bmjopen-2023-074181.supp2Supplementary data

During the analysis phase, we will calculate MAP at each time point using the traditional formula (MAP=diastolic blood pressure+0.33×pulse pressure), and we will calculate the relative threshold (30% MAP reduction from baseline). Based on these, we can determine the occurrence of PIH.

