### Study population

#### Inclusion criteria

Aged 65 or greater and both genders.American Society of Anaesthesiologists (ASA) physical status classification I−III.Undergoing elective non-cardiac surgery under general anaesthesia with tracheal intubation.The duration of the surgery is longer than 30 min.

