### Study outcome

The study outcome is PIH during the first 15 min after anaesthesia induction or before skin incision (whichever occurs first). Preoperative baseline blood pressure will be recorded when patients are comfortably seated in the ward. During anaesthesia induction, patients will be monitored using non-invasive cuff blood pressure at 1 min interval. Hypotension is defined as either a 30% reduction in mean arterial pressure (MAP) from baseline or absolute MAP ≤65 mm Hg. Dual definitions for diagnosis of hypotension (either a relative reduction in MAP or an absolute threshold of MAP) have been used in many recent studies.^20–25^

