#### Intraoperative potential predictors

A total of eight intraoperative potential predictors:

Vital signs including MAP and HR immediately before anaesthesia induction.Dose of anaesthetics used for induction, including propofol, etomidate, ciprofol, esketamine, fentanyl and sufentanil.

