### Sample size estimation

According to previous literature,^5 8^ the incidence of PIH was approximately 35% for patients undergoing elective non-cardiac surgery. Considering a required number of 10 events per variable,^31–33^ we plan to recruit 657 patients for model development and internal validation (657=23×10/0.35). Another 281 patients will be included continuously for model temporal validation. Therefore, the planned sample size will be set to 938 patients.

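### The outcome MAP is rebuilt as diastolic + 0.33 × pulse pressure with no check against a displayed MAP, which can flip PIH labels, mainly at the 65 mm Hg cut-off

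*Protocol article*

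**What the plan says.** The Study outcome section takes pressures by cuff during induction: "patients will be monitored using non-invasive cuff blood pressure at 1 min interval". The outcome has two criteria joined by *or*: "Hypotension is defined as either a 30% reduction in mean arterial pressure (MAP) from baseline or absolute MAP ≤65 mm Hg". The baseline for the first comes from the ward: "Preoperative baseline blood pressure will be recorded when patients are comfortably seated in the ward". The ward device is not described.

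Under Data collection (text after Figure 1), the research assistant copies "values of heart rate (HR) and non-invasive cuff blood pressure (NIBP) in the outcome section during the case when looking at the monitor". The same section then says that in the analysis phase "we will calculate MAP at each time point using the traditional formula (MAP=diastolic blood pressure+0.33×pulse pressure", and that PIH is determined from the result. No reason is given for calculating MAP, and no comparison with a MAP shown by the device is planned.

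MAP is also a candidate predictor twice: ward MAP (Preoperative potential predictors) and "Vital signs including MAP and HR immediately before anaesthesia induction". Neither list says whether that MAP is calculated or read from the device.

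**The concern.** The model's outcome label depends on whether a MAP value crosses a cut-off. The plan obtains that value from systolic and diastolic pressure with one fixed factor for every patient and every minute. If the factor that truly links pulse pressure to MAP differs from 0.33, each calculated MAP is off by an amount proportional to that reading's pulse pressure, and patients near a cut-off get the wrong label.

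Bootstrapping and the temporal cohort cannot reveal this, because both use labels built with the same formula. A displayed MAP, where one exists, would provide a check at almost no cost, and the article does not plan to use it. Discrimination, calibration and the observed incidence all depend on these labels.

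**Working it through.** **Inputs from the article.** MAP formula with factor 0.33; cut-offs of a 30% fall and ≤65 mm Hg; ward baseline; 35% incidence; 23 candidate predictors; 657 patients for development.

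**Inputs assumed.** True factor k, pulse pressure (PP) and all blood-pressure distributions. The article gives none of these.

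**1. The plan's own figure.** 23 × 10 / 0.35 = 657.1, which reproduces 657. This point does not dispute it. It bears on the matter only because the 35% incidence depends on how MAP is obtained.

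**2. Size of the error.** True MAP = D + k × PP and formula MAP = D + 0.33 × PP, where D is diastolic pressure. True minus formula = (k − 0.33) × PP, in mm Hg:

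| k | PP 40 | PP 60 | PP 80 |
|---|---|---|---|
| 0.30 | −1.2 | −1.8 | −2.4 |
| 0.36 | +1.2 | +1.8 | +2.4 |
| 0.40 | +2.8 | +4.2 | +5.6 |
| 0.45 | +4.8 | +7.2 | +9.6 |

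A positive entry means that the formula reads low and PIH is over-called. A negative entry means the reverse.

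**3. Absolute criterion.** For a reading of 95/50, PP = 45. With 0.33, 50 + 14.85 = 64.85, which is PIH. With k = 0.40, 50 + 18 = 68.0, which is not PIH on this criterion.

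**4. Relative criterion, same k at both times.** From 150/75 to 105/50:
- with 0.33: 99.75 to 68.15, a fall of 31.7%;
- with 0.40: 105 to 72, a fall of 31.4%.

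Over the 15 baseline/post-induction pairs tried, moving from 0.33 to 0.40 changed the fall by at most about 1.4 percentage points. The error largely cancels.

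**5. Share relabelled, one k for everyone.** Simulation of 400,000 patients with one post-induction reading each. Ward diastolic has mean 77, SD 9, and ward PP mean 60, SD 14. Post-induction diastolic is the ward value times a factor with mean 0.80, SD 0.12, and PP is the ward value times a factor with mean 0.78, SD 0.15. Patients whose label differs from the 0.33 label:

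| k at both times | ≤65 mm Hg | 30% fall | Combined |
|---|---|---|---|
| 0.30 | 2.9% | 0.5% | 2.2% |
| 0.36 | 2.6% | 0.5% | 1.8% |
| 0.40 | 5.4% | 1.2% | 3.8% |
| 0.45 | 8.3% | 2.0% | 5.8% |

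If the baseline keeps 0.33 and only the post-induction value uses 0.40, 6.6% differ from the all-0.33 labels on the 30% criterion and 7.8% on the combined outcome. Mixing sources within the relative comparison removes the cancellation.

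**6. Share relabelled, k varying between patients (SD 0.04).** Assumed true baseline MAP has mean 96, SD 11. Post-induction MAP is centred at 73, with slope 0.4 on baseline and residual SD 10. PP is 60 (SD 14) at baseline and 48 (SD 12) after induction. True incidence is about 36%.

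| Mean k | Same k at both times | k drawn independently at each time |
|---|---|---|
| 0.33 | 3.1% | 6.7% |
| 0.36 | 4.3% | 7.4% |
| 0.40 | 7.9% | 10.2% |

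At mean k = 0.40 the measured incidence rises from 36% to about 43%.

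**7. In patients.** Of 657, 1.8% to 5.8% is 0.018 × 657 = 12 to 0.058 × 657 = 38. The range 3.1% to 7.9% is 0.031 × 657 = 20 to 0.079 × 657 = 52.

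**The case against.** The formula is prespecified, explicit, reproducible and applied alike to everyone. It contradicts nothing in the article, and no stated figure is wrong. It is one of two accepted ways to obtain MAP, and every k, pulse pressure and SD used above is assumed. This stands: the point is a weakness in a measurement choice, and its size is a range under assumptions.

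A reader might also infer four stronger things that the documents do not support.

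- *A directly measured MAP is thrown away.* The article speaks only of a non-invasive cuff and NIBP. It does not say that the cuff is oscillometric or that MAP is displayed, and the case report form is in a supplement not shown here. All that can be said is that the outcome rule does not use a displayed MAP.
- *Both cut-offs suffer equally, with 7–10% mislabelled.* That range needs k to be drawn afresh at baseline and after induction. If k reflects a stable trait such as arterial stiffness, the error largely cancels in the 30% criterion and the range is about 3–8%. If k does shift at induction, the higher figures become relevant, but the article does not settle that.
- *Labels are distorted according to age or hypertension, and most in this elderly population.* Eligibility is "Aged 65 or greater and both genders", but no pulse pressures are given, and the simulations contain neither age nor hypertension. The error grows with pulse pressure; a link to those predictors is possible but not shown.
- *The calculator will be trained on formula MAP while users enter monitor MAP.* The article ties the formula to determining PIH and leaves the source of the two MAP predictors open. The ambiguity is real; the mismatch is not established.

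**Conclusion.** The point holds in a limited form. The sole outcome rests on a MAP rebuilt with a fixed factor, with no planned check. The error is (k − 0.33) × pulse pressure, its direction depends on whether k is above or below 0.33, and it acts mainly through the ≤65 mm Hg criterion. About 2–6% of patients change PIH status for a common k of 0.36 to 0.45. With k varying between patients but stable within them (SD 0.04, mean 0.33 to 0.40) it is about 3–8%, and more if k changes at induction. The simulations use one post-induction reading per patient rather than a series by the minute, so these figures show the order of magnitude and do not predict this cohort. The case for acting is that the remedy is cheap and the affected quantity is the outcome label itself.

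**What to change.** In the Data collection text after Figure 1 and in the case report form:

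1. Record the MAP displayed by the monitor with each reading and use it for the ≤65 mm Hg criterion.
2. For the 30% criterion, use the same MAP source at ward baseline and after induction: displayed MAP if the ward device shows it, otherwise the formula at both times. A rule that falls back on the formula reading by reading would mix sources and could make this criterion worse.
3. State whether the ward and pre-induction MAP predictors are displayed or calculated.
4. As a sensitivity analysis, report how many patients change PIH status between displayed and formula MAP.
5. The Study design section dates the study December 2022 to August 2023. For patients already enrolled, do this where stored monitor records allow. Otherwise keep the formula throughout and state the limitation.

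The cost is one extra column on the form or one extraction from records. The drawback is that the ward device may show no MAP, in which case the two criteria rest on different sources, each consistent within itself.

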#### Preoperative potential predictors

A total of 15 preoperative potential predictors:

Demographic data including age, gender and body mass index.ASA physical status.Comorbidities including hypertension, diabetes mellitus and the age-adjusted Charlson Comorbidity Index score.Autonomic nervous system function (assessed by symptoms and anamneses).^26 27^Myocardial injury (assessed by anamneses and preoperative examinations).Vital signs in the surgical ward including MAP and HR.Preoperative anxiety assessed by the first four items of the Amsterdam Preoperative Anxiety and Information Scale (APAIS).^28^Preoperative frailty evaluated with the FRAIL (fatigue, resistance, ambulation, illnesses, and loss of weight) scale.^29 30^Preoperative volume of fluid infusion and fasting duration.

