## Introduction

Hypotension is common among patients undergoing surgery and general anaesthesia. It is closely correlated with adverse perioperative outcomes, such as myocardial injury, myocardial infarction, acute kidney injury and death.^1 2^ Accumulating evidence suggested that even short-term hypotension is hazardous to patients during non-cardiac surgery.^3 4^ Approximately 50% of hypotension events occur between anaesthesia induction and surgical incision,^5 6^ which is called post-induction hypotension (PIH). Elderly patients are often frail with comorbidities and low physiological reserve, making them more prone to perioperative hypotension. Compared with intraoperative hypotension related to multiple factors, PIH is mainly attributable to patients’ preoperative conditions and anaesthetic medications, which can be predictable and preventable.

Advanced age, baseline blood pressure, preoperative comorbidities, and type and dose of anaesthetics are associated with PIH.^7 8^ Preoperative volume status and sympathetic activity are also involved in PIH.^9 10^ With further investigation, some PIH prediction models have been developed; however, they are mostly derived from retrospective studies with missing data and limited number of factors, and some studies included patients in a single type of surgery only.^11–14^ In recent years, new predictors have been reported, such as inferior vena cava-related parameters^15–17^ and perfusion index.^18^ Nonetheless, requiring specific equipment or techniques makes those predictors often difficult to be applied in the clinical practice.

Therefore, we designed this prospective cohort study to develop a universal and convenient PIH prediction model for elderly patients undergoing elective non-cardiac surgery. Using this model, we can identify potential hypotension events in advance and take preventive measures to improve anaesthesia management and patient outcomes.

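### Age is a LASSO candidate both in its own right and inside the age-adjusted Charlson index, so it can be dropped more often if comorbidity itself raises the risk of hypotension (minor)

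*Protocol article*

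**What the plan says.** In the protocol article, under Preoperative potential predictors, the first entry is "Demographic data including age, gender and body mass index". The comorbidity entry is "Comorbidities including hypertension, diabetes mellitus and the age-adjusted Charlson Comorbidity Index score". The list is introduced as "A total of 15 preoperative potential predictors", and the next section as "A total of eight intraoperative potential predictors".

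Under Development of the prediction model, the candidates go through LASSO with 10-fold cross-validation repeated 10 times. A multivariable logistic model is then fitted to those selected, so a variable dropped by LASSO does not return. The rule for choosing the penalty (minimum or one-standard-error) is not named. No sentence forces age into the model or deals with its presence in two candidates.

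The Introduction treats both components as risk factors: "Advanced age, baseline blood pressure, preoperative comorbidities, and type and dose of anaesthetics are associated with PIH". The Discussion again names age, citing an earlier prospective study. It also says that the model will show how the main risk factors act on hypotension, and the results are to be displayed in a nomogram and a web calculator.

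**The concern.** An age-adjusted index adds points for age to points for comorbidity. With age also a separate candidate, LASSO has two routes to the same information. If comorbidity predicts the outcome, the index is kept for that reason and brings part of the age effect with it. Age's own term then has less left to explain, and LASSO removes small coefficients first.

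If age is removed and the index stays, one age point must carry the same weight as one comorbidity point. A reader of the selected list or the nomogram would not see age as a factor, although the authors regard it as established. What is at stake is the identification and display of risk factors.

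**Working it through.** **1. Both variables are counted.** Age, gender, body mass index (3); ASA status (4); hypertension, diabetes, age-adjusted index (7); autonomic function (8); myocardial injury (9); ward MAP and heart rate (11); anxiety (12); frailty (13); fluid volume and fasting duration (15). Adding the eight intraoperative candidates gives 15 + 8 = 23. Under Sample size estimation the article assumes that "the incidence of PIH was approximately 35% for patients undergoing elective non-cardiac surgery" and continues "Considering a required number of 10 events per variable". So N = 23 × 10 / 0.35 = 657.1, which reproduces the stated 657.

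**2. Mechanism.** Let b be the log-odds per year of age, g the log-odds per comorbidity point, and k the age points per year. The age-adjusted index is approximately the plain index + k × age + a constant. Apart from the constant and the banding of age,

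b × age + g × index = (b − g × k) × age + g × (age-adjusted index).

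For b > 0, age's own coefficient shrinks toward zero only if g is positive and g × k does not greatly exceed b.

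**3. Assumptions (none is in the article).** One age point per decade from age 50, capped at 4, so k is about 0.1 (a little less, because of the cap). Age has mean 72.4 and SD 5.3, with enrolment from 65. Age log-odds are 0.15, 0.25 or 0.35 per SD; comorbidity log-odds are 0, 0.1 or 0.2 per point. Five other independent predictors have effects. Example: with 0.15 per SD and g = 0.2, the coefficient left for age is 0.15 − 0.2 × 0.1 × 5.3 = 0.15 − 0.106 = 0.044 per SD.

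**4. Simulation.** n=657, 23 standardised candidates, about 35% events, logistic LASSO with a single 10-fold cross-validation, 150 runs per row. Each data set was fitted with both forms of the index. Excess means the additional percentage points by which age is dropped with the age-adjusted form.

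| Age effect per SD | Comorbidity effect per point | Age's own coefficient left | Age dropped, age-adjusted index | Age dropped, index without age points | Excess, minimum penalty | Excess, one-SE rule |
|---|---|---|---|---|---|---|
| 0.15 | 0 | 0.150 | 25% | 21% | 4 | 0 |
| 0.15 | 0.1 | 0.097 | 33% | 19% | 14 | 11 |
| 0.15 | 0.2 | 0.044 | 49% | 18% | 31 | 25 |
| 0.25 | 0 | 0.250 | 2% | 2% | 0 | 0 |
| 0.25 | 0.1 | 0.197 | 7% | 1% | 6 | 12 |
| 0.25 | 0.2 | 0.144 | 17% | 1% | 16 | 32 |
| 0.35 | 0 | 0.350 | 0% | 0% | 0 | 0 |
| 0.35 | 0.1 | 0.297 | 0% | 0% | 0 | 2 |
| 0.35 | 0.2 | 0.244 | 1% | 0% | 1 | 12 |

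For the first row, the standard error of the difference, ignoring pairing, is √(0.25 × 0.75/150 + 0.21 × 0.79/150) = 0.049. The 4 points are therefore within simulation error.

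**5. Sensitivity, 120 runs each, minimum penalty.** With fewer comorbidities (mean 0.5 points) and g = 0.2, age was dropped in 42.5% vs 25.8% (age effect 0.15) and 18.3% vs 4.2% (0.25). With g = 0 the excess was 5 points (0.15) and 2.5 points (0.25). With g = −0.1 there was no excess (3% vs 4%).

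**6. Predictive performance.** In the same five scenarios, test AUC of the refitted model was 0.667 vs 0.667, 0.673 vs 0.673, 0.671 vs 0.671, 0.672 vs 0.673 and 0.665 vs 0.665. One reason is visible in the row with the largest excess: 0.15 per SD is 0.15 × 10/5.3 = 0.28 per decade, not far from the 0.2 per comorbidity point, so tying the two weights costs little.

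**7. Other assumed settings.** With 0.02 per year of age, 0.2 for diabetes, 0.15 per other comorbidity point and age points of 2, 3 or 4 (300 runs), age was retained in 36% vs 54%, a difference of 18 points (SE 2.6). That age effect is weaker than any in the table: 0.02 × 5.3 = 0.11 per SD. A further check with 60 runs per scenario gave retention of 45% vs 85% and 85% vs 98% with a comorbidity effect and 77% vs 80% without, again with no change in AUC or prediction error.

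**The case against.** The strongest defence is that the study's purpose is prediction, and prediction does not suffer. When age is dropped and the index kept, age still acts through the index. The overlap is also moderate: correlations of 0.42 and 0.58 give variance inflation of 1/(1 − 0.42²) = 1.21 and 1/(1 − 0.58²) = 1.51. The choice of index form could be called a coding preference, and an analysis plan that is not shown might deal with correlated candidates. The point about prediction stands and is why the severity is low. The appeal to an unseen plan carries less weight, because the article itself fixes the candidate list and its count.

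A reader might infer more than the article supports:

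- **That age will be lost.** This needs a positive comorbidity effect and a weak to moderate age effect. The Introduction makes the first plausible, but the article gives no size for either.
- **That age is counted twice in the nomogram if both terms stay.** The final model is a joint logistic refit, so the coefficients are mutually adjusted. By the identity in step 2 it is, apart from banding, the same model in another parameterisation.
- **That the model cannot separate age from comorbidity.** With both terms retained it can, for the same reason. Only when one is dropped are the weights tied.
- **That diabetes must come out of the index.** The index's item list is not in the article, and the case report form is not shown. This is a question for the authors to check.

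**Conclusion.** The point holds in a conditional form and is minor. Age enters the candidate set twice, and the text does nothing about it. If comorbidity raises the risk and the age effect is weak to moderate, age is dropped 6 to 31 percentage points more often at the minimum penalty in the 150- and 120-run scenarios (11 to 32 under the one-standard-error rule). With no comorbidity effect the excess at the minimum penalty is 0 to 5 points; with a strong age effect it is 0 to 1 point (2 to 12 under the one-standard-error rule when comorbidity has an effect).

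These sizes depend on the assumed effects, age distribution and age points, and on a single rather than repeated cross-validation. The direction follows from the algebra. No loss of discrimination was found. The consequence is confined to which risk factors are reported as selected and how their separate effects appear in the nomogram.

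**What to change.** Under Preoperative potential predictors, replace the age-adjusted index by the Charlson index without age points, and keep age as its own term. Carry the same coding through the LASSO, the nomogram and the web calculator, and settle it before the selection is run.

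Age is recorded for every patient, so the age points can be subtracted from the recorded score at analysis. One candidate replaces another: the count stays at 15 + 8 = 23 and N at 657. No new data or patients are needed. The authors could also check, from their own definition of the index, whether diabetes appears both there and as a separate candidate.

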#### Intraoperative potential predictors

A total of eight intraoperative potential predictors:

Vital signs including MAP and HR immediately before anaesthesia induction.Dose of anaesthetics used for induction, including propofol, etomidate, ciprofol, esketamine, fentanyl and sufentanil.

